### 2.11. Measures

All self-report parent and child measures were administered using Research Electronic Data Capture (REDCap) electronic data capture tools [93,94] hosted at the University of Washington. A list of measures with descriptions and timings of assessments can be found below and in Table 4.

#### 2.11.1. Demographic Questionnaire

A demographic questionnaire created by our team asked questions about parent and child age, gender, ethnicity, and race. Parent education, marital status, employment, and household composition were also assessed. The questionnaire also asked about child health insurance, number of languages spoken, child birth history, breastfeeding history, number of child’s siblings, % of food the child eats that are organic and genetically modified, child height and weight, and child education (grade in school, type of school, and school enrollment).

#### 2.11.2. Youth/Adolescent Questionnaire (Diet Diary)

At the time of the stool collection, all participants will complete a 3-day diet diary using the Youth/Adolescent Questionnaire validated in this age group [95]. This questionnaire asks parents to record everything their child ate and drank each day (name of food, quantity/amount consumed, how prepared, where prepared [restaurant vs. home] and time of eating). Responses were reviewed by the study dietitians who asked parents for further clarification when needed.

#### 2.11.3. Pain and Stool Diary (Primary Outcome Measure: Pain Frequency and Severity)

A 14-day pain and stool diary will be completed by the child with help from their parent. The diary asks whether pain was experienced each day. If yes, additional questions are asked about pain severity (rated using a numeric rating scale (0–10, with 0 = “none” and 10 = “all the time”) that has been validated for measuring abdominal pain in children) [96,97], and pain frequency (how many times pain occurred). For morning, afternoon, and evening pain, questions are asked about pain duration, pain location, and interference with activities. Stooling questions (how many times child passed stool each day, stool consistency [Bristol Stool Chart], timing of stools, and whether pain occurred with stool) are also included. Additional questions (0–10 scale, with 0 = “none” and 10 = “all the time”) include things that happen while eating or right after eating (nausea, feeling full, burping, and bloating), as well as other symptoms (pain or burning above the belly button, passing gas, heartburn, fatigue, and headache).

#### 2.11.4. Pediatric Quality of Life Inventory (PedsQL; Primary Outcome Measure)

Health-Related Quality of Life (HRQOL) will be assessed using the Pediatric Quality of Life Inventory (PedsQL) 4.0 generic core scales [98,99,100]. The PedsQL is the most widely used measure of pediatric HRQOL, consisting of 23 items. Items are scored on a 5-point Likert scale ranging from 0 (never a problem) to 4 (almost always a problem). Total scores range from 0 to 100 with 100 indicating excellent HRQOL. A psychosocial health summary score also is calculated as a sum of the emotional, social, and school functioning subscales. The generic core scales have adequate feasibility, reliability, and validity in children with DGBIs [7,99].

#### 2.11.5. Children’s Sleep Habits Questionnaire (CSHQ; Secondary Outcome Measure)

Sleep problems will be screened using the 45-item Children’s Sleep Habits Questionnaire (child and parent form), one of the most widely-used and validated tools to screen for pediatric sleep problems in school-age children [101]. Sleep behavior is measured on 33 items scored as usually (5–7X/week), sometimes (2–4X/week), and rarely (0–1X/week). A total score ≥ 41 discriminates between children with/without sleep problems (sensitivity 0.80; specificity 0.72) [101].

#### 2.11.6. Healthcare Utilization and Missed School Days (Secondary Outcome Measures)

Parents will be asked to retrospectively provide the number of visits to a healthcare provider for abdominal pain and/or any illness. Increased school absenteeism is common in children with DGBI. Thus, missed school days often are used as a measure of functional disability [102]. Parents will retrospectively provide the number of school days and other activities missed by their child in the previous 3 months due to pain and/or illness.

#### 2.11.7. Heart Rate Variability (HRV)

Ambulatory electrocardiogram Holter monitors will be used to measure HRV over 20 min while the children are lying quietly [23,81,103,104,105]. All HRV measurements will be obtained at the same time of day. GE Healthcare Holter 3-channel SEER 1000 Recorders (GE Healthcare, Wauwatosa, WI) will be used, and the results will be processed using GE CardioDay 2.5 software.

#### 2.11.8. GI Permeability

All participants will undergo GI permeability testing [8,106]. Participants will fast overnight and urinate upon arising. They will then drink a 100 mL solution containing lactulose (5 g) and mannitol (1 g) followed by 240 mL of water after which time they fast for 4 h. Urine will be collected hourly for the first 4 h and then all urine passed between 4 and 24 h will be combined and analyzed (increased urinary lactulose/mannitol ratio indicates increased small intestinal permeability) [107,108,109].

#### 2.11.9. Gut Microbial Composition

A stool sample will be collected as we have described using a container that seals and serves as its own storage system, so the handling of the stool is not required (Fischer Scientific Inc., Pittsburgh, PA, USA) [39,110]. Bacterial DNA will be extracted using the PowerSoil DNA Isolation kit (MO BIO Laboratories, Carlsbad, CA, USA), with the Human Microbiome Project’s modifications to the manufacturer’s protocol [111]. Whole Genome Shotgun (WGS) metagenomic sequencing will allow the identification of bacterial taxa (species) as well as their metabolic functional potential. Although samples will be sequenced at various time points throughout the study (and thus, on multiple sequencing runs), repeated sequencing of the same specimens has shown, in our hands, to result in >99% concordance between taxonomic profiles (unpublished data). All sequence data will be deposited in the NCBI dbGaP, and detailed sequence analysis protocols will be provided in all related publications.

#### 2.11.10. Fecal Granins

Stool collected for microbiome analysis also will be used to measure chromogranin A and secretogranin III—the granins our preliminary data suggest are elevated in children (as in adults) with DGBIs, and which correlate with abdominal pain symptoms [112,113].

#### 2.11.11. Pain Response Inventory (PRI)

The Pain Response Inventory [114] consists of 31 items that assess children’s coping responses to recurrent pain. It assesses 3 broad coping factors (Active, Passive, and Accommodative). Items are scored on a 0–4 scale (0 = never to 4 = always). It has been validated in pediatric samples and has demonstrated good internal consistency and reliability [114].

#### 2.11.12. Symptom Checklist 90-Revised (SCL-90-R)

The Symptom Checklist 90-Revised is a widely used questionnaire for measuring a range of psychological and psychiatric symptoms [115,116]. It involves 9 dimensions, including somatization, depression, and anxiety. It has been validated in child and adolescent populations, and has demonstrated acceptable internal and test–retest reliability.

#### 2.11.13. Pain Catastrophizing Scale (PCS)

The Pain Catastrophizing Scale [117,118] measures dimensions of rumination, magnification and helplessness that are subsumed under the higher-order construct of pain catastrophizing. The PCS has been validated in children and adolescents, including those with chronic pain, and has demonstrated acceptable reliability [119,120].

#### 2.11.14. Pain Behavior Checklist (PBCL)

The 17-item Pain Behavior Checklist [121] measures pain behaviors across four domains: distorted ambulation, affective distress, facial/audible expressions, and seeking help. The PBCL has been used in prior studies of children with functional abdominal pain and has adequate reliability [70].

#### 2.11.15. Tanner Stage Questionnaire

The Tanner Stage Questionnaire [122,123] assesses the physical development of children into adolescence and then adulthood. It defines physical measurements of development based on primary and secondary sex characteristics, indicating pubertal stages.

#### 2.11.16. Behavior Assessment System for Children-3 (BASC-3)

The BASC-3 [124] includes both parent and child/adolescent self-report of a child’s emotional and behavioral functioning. Item responses are converted into summary scales and indexes. For the parent report, there are two summary scales (clinical and adaptive scales, including anxiety, attention problems, depression, and somatization; content scales include anger, emotional self-control, executive functioning, and resiliency) and two indexes (clinical index includes ADHD probability, clinical probability, and functional impairment; executive functioning index includes attentional, behavioral, and emotional control, and problem-solving). Composite scores include behavioral symptoms, externalizing problems, internalizing problems, and school problems. For the child report, there are two summary scales (clinical and adaptive scales, including anxiety, depression, interpersonal relations, self-esteem, and somatization; content scales include anger control, ego strength, and mania), one index (functional impairment), and composite scores (includes emotional symptoms, internalizing problems, and a total score). Validity and reliability have been well established [124,125].

#### 2.11.17. Treatment Credibility Scale

Treatment credibility will be assessed with a brief survey created by our team. Items include questions about how confident the parent is that this treatment will be successful in reducing their child’s abdominal pain, if they would recommend this treatment to a friend, and if treatment would help them manage their child’s abdominal pain. Items range from 0 (“not at all”) to 9 (“very much”).

#### 2.11.18. Sleep Self Report (SSR)

The child-report Sleep Self Report is a 26-item retrospective survey that assesses the frequency of occurrence of constructs such as bedtime resistance, night awakenings, sleep duration, and daytime sleepiness in the past week [126]. Each item is rated on a 3-point response scale (rarely, sometimes, usually) with a higher score indicating more sleep problems. Items are summed for a total score. Internal consistency and reliability has been reported at 0.88 [126].

#### 2.11.19. ROME-IV Diagnostic Questionnaire on Pediatric Functional Gastrointestinal Disorders (R4PDQ)

The R4PDQ includes child self-report and parent proxy-report forms assessing presence, frequency, and severity of gastrointestinal (GI) symptoms (including pain, bloating, stooling, nausea/vomiting) [127]. Item response scales are varied—some items have a simple “yes/no” response option, whereas others are on a Likert Scale (“never” to “always”). Item scoring derives summary scores that indicate whether a child meets criteria for various functional GI disorders including Functional Dyspepsia, Irritable Bowel Syndrome, and Functional Abdominal pain.

#### 2.11.20. Adults’ Responses to Children’s Symptoms (ARCS; Protect and Minimize Only)

Parental solicitousness in response to pain behavior will be measured using the Protectiveness subscale of the Adults’ Responses to Children’s Symptoms [128]. All 11 items are rated on a 0–4 scale, with higher values indicative of greater solicitousness.

#### 2.11.21. Pain Beliefs Questionnaire (PBQ)

The Pain Beliefs Questionnaire [129,130] 20-item threat scale includes items assessing the perceived duration, frequency, and seriousness of the abdominal pain condition, as well as the intensity and duration of individual pain episodes. Items are rated on a 0–4 scale (0 = not at all true to 4 = very true).

#### 2.11.22. Functional Disability Inventory (FDI)

The Functional Disability Inventory [131] measures the degree to which children experience difficulties in physical and psychosocial functioning. Respondents are asked to rate how much physical difficulty they experienced doing everyday activities such as walking up stairs or doing something with a friend. Responses range from 0 (no trouble) to 4 (impossible). A total score is derived by summing the ratings for each item. Higher scores indicate greater disability. The FDI has been validated in several pediatric populations, including those with chronic pain, and has demonstrated adequate reliability [132,133,134].

### 2.12. Participant Retention and Follow-Up

Participants will receive automated assessment survey invitations and reminders. Research coordinators will send reminders if assessments are not complete, until the completion of the assessment period. We will use a database checklist to ensure that all study procedures are being followed (including consent) and that all surveys are being completed according to schedule. Study staff will review study participant data and monitor parent responses. Participants will also receive gift card incentives for completing baseline and follow-up assessments. All study questionnaires will be completed online so that participants may complete them at a time and place that is convenient for them.

### 2.13. Data Management

All survey data will be collected from parents online using REDCap electronic data capture tools hosted at the University of Washington. REDCap is a secure, web-based software platform designed to support data capture for research studies, providing (1) an intuitive interface for validated data capture; (2) audit trails for tracking data manipulation and export procedures; (3) automated export procedures for seamless data downloads to common statistical packages; and (4) procedures for data integration and interoperability with external sources [95]. Research coordinators will track assessment completion regularly, monitor for any missing data, and follow up with participants when missing data are identified. Research coordinators will also use REDCap alerts, reports, and queries to minimize missing data and ensure accuracy. Additionally, study staff will monitor for data irregularities such as skip patterns and out-of-range data and completion times. The REDCap database will require online sign-in with a username and password assigned to individual study staff; all data stored in REDCap will be retained on a secure server accessible only to study staff. The scoring of study measures will be done via syntax to minimize errors.

### 2.14. Confidentiality

The subject’s identity, research records, and personal health information will be safeguarded using password-protected servers. The primary source of data will be questionnaires, which will be stored electronically in REDCap. All data will be coded with a unique participant ID. The software will be hosted on a secure, HIPAA-compliant server. Only the research team and the Baylor College of Medicine IRB will be able to access the participant data and information collected from this study. All research data will be de-identified at the earliest possible opportunity to promote data sharing.

### 2.15. Statistical Methods

The primary outcome variables at 3 months after completing treatment will be mean number of pain episodes/week and QOL. An analysis of covariance model will be fit, with pain frequency and QOL as the outcome variables, and treatment group (CBT or LFD) and biomarker group (abnormal versus normal) as factors, using baseline pain frequency and QOL as covariates. The interaction between treatment group and biomarker group will be included in the model, and the test of this interaction term will be the primary test of interest. If this term is zero then the null hypothesis is true and the effectiveness of CBT relative to the LFD is the same in the two biomarker groups. If the interaction is significantly different from zero, the relative effectiveness of CBT versus the LFD differs between the two biomarker groups. A general overview of this analytic approach can be found in Figure S1 in the Supplementary Materials. We will test the effect of sex using the above-described analysis of covariance model, wherein sex will be used instead of biomarker group as a factor. Similar analyses will be done for the additional secondary outcome measures of healthcare utilization, missed school days, and sleep. We will examine pain and QOL trajectories. However, 3 months is specified as the primary outcome time because if the effect does not last until at least 3 months, it is less impactful clinically, and there will be fewer missing data at 3 than at 6 months.

Baseline pain frequency/QOL potentially could confound the interaction effect being tested—treatment effectiveness (improvement with CBT minus improvement with the LFD) may be greater for those with higher baseline pain frequency/lower QOL. If so, the interaction between treatment group and baseline pain frequency also will be included in the model.

Two approaches will be considered regarding missing data. The first uses a mixed model to analyze all three time points together. This allows some time points to have missing data, but still gives unbiased estimates if data are missing at random, conditional on the data that are not missing. The second will be multiple imputations, which imputes missing data based on the data not missing.

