### 1.3. Altered GI Microbiome Composition

Studies also suggest that the composition of the GI microbiome differs between DGBI patients and healthy individuals [40,41]. In a small group of children with IBS (*n* = 22), composition was related to severity of abdominal pain symptoms; this parallels findings in adults with DGBI [40,41,42,43,44,45,46,47]. Visceral hyperalgesia is a common finding in children and adults with DGBI that may be related to GI microbiome composition via the upregulation of immune responses, which, in turn, can increase gut permeability. Gut inflammation, the degree of which can be modified by gut bacteria and which can also be gender-dependent, can affect the function of smooth muscle and enteric nerves, resulting in dysmotility [48,49,50,51,52]. These data underscore the potential contribution of the GI microbiome not only to abdominal pain but also to other gut alterations (increased GI permeability and inflammation) found in some patients with DGBI. However, discrepancies exist among studies as to the strength of the relationship between symptoms (abdominal pain, bowel pattern) and differences in the gut microbiome. Thus, the links between microbiome signatures and symptoms of DGBIs remain to be fully elucidated.

The potential relationship between gut microbiome composition and responsiveness to treatment is varied; CBT has received scant attention in the adult and pediatric literature [53,54]. For example, Chumpitazi et al. showed in children that baseline microbiome composition predicted response to an LFD, as well as to a challenge with the FODMAP fructan [55,56]. Discrepancies among studies investigating the potential relationship between gut microbiome composition, symptoms, and psychological distress and response to treatment (CBT, LFD) are likely due to differences in patient populations, bacterial sequencing methodology, and the data analytic approaches used.

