### 2.4. Sample Size

The sample size will be 100 subjects per treatment group (i.e., 200). Table 2 shows how power depends on effect size, which is unknown, and also the fraction of subjects in the abnormal biomarker subgroup. Power for detecting an interaction should be good if the effect size is ≥0.9. In our prior study delivering CBT to adults with DGBI and measuring biomarkers (*n* = 85), the effect sizes observed were 1.12 for LF/HF ratio and 0.76 for high-frequency HRV [81]. Given our proposed sample size is >2-fold greater than in our previous studies and 30% of children with DGBIs have increased gut permeability [8], we should be able to detect potential differences between groups.

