### 2.6. Randomization

Group allocation will be determined using a computer-generated algorithm with equal assignments to each study arm. Subjects will be stratified based on age (7–9 vs. 10–12), sex, baseline pain (mean pain frequency (≤50% of the rated intervals or >50% of the rated intervals, as reported on the baseline 2-week pain diary)), QOL, and presence/absence of abnormal physiological biomarkers.

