## Figures and Tables

**Figure 1 jcm-14-03185-f001:**
[figure not shown]
Study Recruitment Flow and Condition Allocation.

**Table 1 jcm-14-03185-t001:** Eligibility criteria.

Inclusion Criteria
Child age 7–12 years Medical evaluation negative for organic cause of abdominal pain and symptoms meeting the definition of a DGBI per pediatric Rome IV criteria. Parent and child speak English
Exclusion Criteria
Children who have had: ○ Past bowel surgery ○ Organic GI disorder ○ Serious chronic medical condition (i.e., diabetes) ○ Weight and/or height < 2 SD for age ○ Chronic condition(s) with GI symptoms (e.g., cystic fibrosis) ○ Autism Spectrum Disorder ○ Significant developmental delay ○ Psychosis and/or bipolar disorder ○ Have been treated with antibiotics/probiotics within 1 month (possible gut microbiome effects) ○ Children who are currently using the LFD or are receiving CBT

**Table 2 jcm-14-03185-t002:** Relationship between power and effect size.

Effect Size *	Power % Fraction ^#^ = 0.5	Power % Fraction = 0.33	Power % Fraction = 0.25
0.6	56	51	45
0.7	69	64	57
0.8	80	75	68
0.9	89	85	78
1.0	94	91	86

* Effect Size = magnitude of the interaction term divided by the within group standard deviation. ^#^ Fraction of subjects who fall within the abnormal group or the normal group, whichever is smaller.

**Table 3 jcm-14-03185-t003:** Schedule of enrollment, interventions, and assessments.

Timepoint	Enrollment	Baseline t1	Randomization	Treatment	Post-Treatment *				
					t2	t3	t4	t5	t6

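### The primary ANCOVA leaves out age group and sex, both stratification factors, and no stated model holds the biomarker and sex interactions together

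*Protocol article*

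**What the plan says.** Section 2.6 of the protocol article lists five stratification factors. It opens with "Subjects will be stratified based on age (7–9 vs. 10–12), sex, baseline pain" and goes on to QOL and the presence or absence of abnormal biomarkers.

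Section 2.15 then names the terms of the primary model: "treatment group (CBT or LFD) and biomarker group (abnormal versus normal) as factors, using baseline pain frequency and QOL as covariates". The treatment-by-biomarker interaction is included, and its test is the primary test. Three of the five stratification factors are therefore represented: pain and QOL through their baseline values, and biomarker status as a factor. Age group and sex are not.

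For sex, section 2.15 reuses the same model, "wherein sex will be used instead of biomarker group as a factor". The biomarker term and its interaction drop out of that analysis.

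On power, section 2.4 states "Power for detecting an interaction should be good if the effect size is ≥0.9", and Table 2 gives the supporting figures.

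**The concern.** There are two separate issues.

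**Omitted stratification factors.** Stratified allocation balances the arms on age group and sex. If these factors predict pain or QOL, the treatment contrasts already vary less from sample to sample than an unadjusted model assumes. The model leaves the variance they explain in its error term, so its standard errors are too large, its confidence intervals too wide and its test a little below nominal size.

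**No joint model.** The plan examines two candidate moderators, biomarker status and sex, each in a model without the other. If they are associated in this population and one truly moderates the treatment effect, the other will seem to moderate as well. The article gives some reason to take this seriously. Section 1.3 says "Gut inflammation, the degree of which can be modified by gut bacteria and which can also be gender-dependent". Section 2.15 itself worries that baseline pain or QOL could confound the interaction, and would then add a treatment-by-baseline-pain term. It does not extend that reasoning to sex, although it tests sex as a moderator.

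At stake are a small amount of precision on the primary test and the reading of any sex-by-treatment or biomarker-by-treatment finding.

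**Working it through.** **Inputs from the article.** The total is 200: "The sample size will be 100 subjects per treatment group (i.e., 200"). Effect size in Table 2: "Effect Size = magnitude of the interaction term divided by the within group standard deviation". Biomarker fraction *f*: "Fraction of subjects who fall within the abnormal group or the normal group, whichever is smaller", at 0.5, 0.33 and 0.25.

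**Assumptions (not in the article).** Two-sided alpha of 5%; R² (the share of the model's residual variance explained by age group and sex) of 2, 5 or 10%; for the simulations, 60% girls, *f* = 0.33, and biomarker prevalence differing by 0 to 30 points between the sexes.

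**Step 1: reproduce Table 2.** SE/SD = √(4 / (N·f·(1−f))); power = Φ(effect/SE − 1.96). At *f* = 0.33, SE = √(4/(200 × 0.33 × 0.67)) = 0.301, and an effect of 0.9 gives Φ(2.99 − 1.96) = 84.9%, against 85% in the table. At *f* = 0.5 and 0.25 the results are 88.9% and 78.7%, against 89% and 78%. All 15 cells agree within one point.

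**Step 2: power after adjustment.** Multiply the variance by (1 − R²). Effect 0.9:

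| *f* | R² = 0 | 2% | 5% | 10% |
|---|---|---|---|---|
| 0.5 | 88.9 | 89.5 | 90.4 | 91.8 |
| 0.33 | 84.9 | 85.6 | 86.7 | 88.4 |
| 0.25 | 78.7 | 79.5 | 80.7 | 82.8 |

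The gain is 0.6 to 4.1 points. As equivalent sample size, 1/(1 − R²) − 1 is about 2, 5 and 11%.

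This is the upper end. If stratification balances the arms fully, the unadjusted estimate already has the smaller variance and only its stated SE is too large. Unadjusted power is then Φ((0.9 − 1.96·SE)/(SE·√(1−R²))). At *f* = 0.33 and R² = 10%: (0.9 − 1.96 × 0.3008)/0.2853 gives 86.2%, against 88.4% adjusted, a gain of 2.2 points and not 3.5. In simulation with age and sex effects of 0.3 SD each, power rose from 82.6% to 83.7%.

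**Step 3: size of the unadjusted test.** 2·(1 − Φ(1.96/√(1 − R²))) gives 4.8, 4.4 and 3.9% for R² of 2, 5 and 10%. Simulation under stratified allocation gave 4.5% with age and sex effects of 0.3 SD each, and 3.5% with 0.5 SD each. With both factors in the model it gave 5.0% and 4.7%.

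**Step 4: sex model without biomarker group.** Shift in the sex-by-treatment term = (prevalence in girls − prevalence in boys) × biomarker interaction. With 20 points and 0.9 SD: 0.20 × 0.9 = 0.18 SD. Simulation with a 0.9 SD biomarker interaction and no sex interaction of its own:

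| Prevalence difference | Sex-by-treatment estimate, sex-only model | Rejection, sex-only | Rejection, joint model |
|---|---|---|---|
| 0 | about 0 | 5% | 6% |
| 10 points | 0.10 SD | 6% | 5% |
| 20 points | 0.18 SD | 9% | 5% |
| 30 points | 0.28 SD | 13% | 5% |

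The joint model's estimate is about 0 in every row.

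**Step 5: the reverse direction.** With a true sex interaction of 0.9 SD, no biomarker interaction and a 20-point prevalence difference, the stated primary model shows a biomarker interaction of 0.19 SD. Adding age and sex as main effects leaves it at 0.19. Adding treatment × sex brings it to about 0.

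**The case against.** Several objections stand.

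- The precision loss is modest, its size rests wholly on an assumed R², and the error is conservative, so no false-positive risk is added through omitted main effects. The model already carries the baselines of both primary outcomes, and the age range is narrow.
- The sex analysis is a separate model. Swapping the factor there leaves the primary estimate and test unchanged.
- Whether relative effectiveness differs between boys and girls, whatever their biomarker status, is a legitimate marginal question, and the sex-only model answers it. On that reading the 0.18 SD is a real difference between the sexes. It misleads only if taken as independent of biomarker status, which section 2.15 does not claim.

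A reader might infer that the plan does confound the two interactions. The article does not support that. It gives no biomarker prevalence by sex, and the remark in section 1.3 concerns gut inflammation, which is not among the biological measures in Table 4. With no association, the bias is zero. A reader might also infer that the omission matters because the trial is short of power. Table 2 reproduces, and nothing in this point shows it to be wrong.

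The objection that a condensed article may leave covariates to a later plan carries less weight. Section 2.15 names the model's factors and covariates and states the substitution outright, so this is a comment on what is written.

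**Conclusion.** The point holds as a modest improvement to the analysis and not as a flaw that invalidates the primary result.

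Age group and sex stratify the randomisation and are missing from the stated primary model. Including them is worth about 1 to 4 power points at an effect of 0.9 if R² is 2 to 10%, and less within that range where stratification has already balanced the arms. It also brings a slightly conservative test back to about 5%.

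The absence of a joint model is an interpretive gap that depends on two conditions: an association between sex and biomarker status, and at least one real interaction. If both hold, the stated models cannot separate the two moderators. A 10 to 30 point prevalence difference with a 0.9 SD biomarker interaction moves the sex-by-treatment term by about 0.1 to 0.3 SD. The direction of these effects is certain under the stated conditions. Their size in this trial cannot be found from the article.

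**What to change.** 1. In section 2.15, add age group and sex as covariates to both primary models (pain frequency and QOL). With 200 children and six parameters in the stated model, residual degrees of freedom fall from 194 to 192. Both variables are already recorded for randomisation.
2. Add a model that keeps treatment × biomarker and adds treatment × sex, with the same covariates. This costs one further degree of freedom (191). Use it for any claim that sex moderates independently of biomarker status, and report its biomarker interaction as a sensitivity check on the primary result. The main effects in item 1 do not do this job.
3. The sex-only model may stay, described as the marginal comparison between boys and girls. Report biomarker prevalence by sex beside it, so that readers can judge how far the two moderators overlap.

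The change is to wording only. It should be made before outcomes are analysed by arm, so that the covariate choice is not open to dispute afterwards.
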